#### 2.9.1. Primary outcome

Tinnitus loudness is a main symptom of tinnitus. The primary endpoint of our study will be the change in NRS score for tinnitus loudness from baseline to treatment completion (week 5). Changes in the mean NRS score for tinnitus from baseline to week 10 (5 weeks after treatment completion) will also be assessed. The NRS for the loudness of tinnitus is a widely used measurement for tinnitus.^[2]^ Subjects will rate the loudness of tinnitus using an 11-point NRS (0 − 10) with 0 indicating “no tinnitus”, and 10 indicating “maximum intolerable tinnitus”. The higher the score, the greater the tinnitus loudness and its effect.

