### 2.13. Statistical analysis

#### 2.13.1. Sample size calculation

The sample size calculation will be based on the primary outcome measure of the NRS score of the loudness of tinnitus (0 − 10 points) and performed using OpenEpi.^[35]^ An estimation of the between-group difference and standard deviation is necessary because of the lack of similar comparable studies. In this study, we assume that similar differences in the NRS score of tinnitus loudness will be detected between the EA and waitlist control groups or the EAWN and waitlist control groups. We presume that a clinically significant difference of mean 2-point reduction and standard deviation of 2.49 in the NRS score of tinnitus loudness is detected based on previous studies^[36,37]^ and expert opinion. Using a 2-sided test, an alpha value of 0.05, and a power of 80%, it is estimated that 25 subjects will be required per study group. Considering a 20% attrition rate, the sample size for each group will be 30 subjects, which implies a total sample size of 90 subjects for the entire trial.

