#### 2.13.2. Statistical method and analysis

Statistical analysis of the collected data will be performed using IBM SPSS Statistics 27 (IBM Corp, Armonk, USA). An intention-to-treat approach will be used in this study. All randomized subjects will be included in the analysis, regardless of whether they received treatment. In addition, interim analyses will not be performed.

Descriptive statistics will be used to summarize participants baseline characteristics by group using mean (standard deviation), median (interquartile range), or number (percentage) as appropriate. All measurement data will first be assessed using normality tests. One-way analysis of variance or Welch analysis of variance will be used for comparison among the 3 groups for continuous variables. Categorical variables will be compared using the Pearson chi-squared test (or Fisher exact test).

Analyses of the primary and secondary continuous outcome variables among the 3 study groups (EA, EAWN, and waitlist control) overtime (baseline, weeks 5 and 10) will be performed using linear mixed models for repeated measures analysis, with treatment, time point, and interaction between treatment and time point included as fixed effects, within-person correlation modeled as a random effect, and age and tinnitus duration adjusted as covariates in the model. Missing data will be processed using the mixed effects model, assuming missing at random. Significant results (significant interaction, time × study groups) will be subject to post hoc tests to determine which group scores differently. Mean differences at weeks 5 and 10 will be estimated by the treatment × time interaction term, with associated 95% confidence intervals and *P* values.

Comparisons between the EA and EAWN groups for the adverse event rate among the 3 groups will be evaluated using the Pearson chi-squared test (or Fisher exact test).

The results will be considered statistically significant at a probability level of *P* < .05 with a 2-sided test throughout the analysis. In post hoc tests, we will employ the Bonferroni correction method and appropriately adjust the overall level of significance for multiple primary and secondary outcomes at different time points.

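### Section 2.13.2 gives two routes to a week-5 conclusion: one conditional on a 4-df group-by-time interaction that does not isolate week 5, one unconditional. It does not say which decides.

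*Protocol article*

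**What the plan says.** All references are to the protocol article.

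- **Endpoint (2.9.1).** "The primary endpoint of our study will be the change in NRS score for tinnitus loudness from baseline to treatment completion (week 5"). Week 10 is also assessed.
- **Sample size (2.13.1).** The calculation is pairwise. Its working assumption reads: "similar differences in the NRS score of tinnitus loudness will be detected between the EA and waitlist control groups or the EAWN and waitlist control". The effect entered is a "clinically significant difference of mean 2-point reduction and standard deviation of 2.49 in the NRS score of tinnitus loudness", at two-sided alpha 0.05 and 80% power, giving 25 per group.
- **Model (2.13.2).** A linear mixed model is fitted "among the 3 study groups (EA, EAWN, and waitlist control) overtime (baseline, weeks 5 and 10"). Its terms are described so: "with treatment, time point, and interaction between treatment and time point included as fixed effects".
- **Conditional route (2.13.2).** "Significant results (significant interaction, time × study groups) will be subject to post hoc tests to determine which group scores differently".
- **Unconditional route (2.13.2, next sentence).** "Mean differences at weeks 5 and 10 will be estimated by the treatment × time interaction term, with associated 95% confidence intervals and". The sentence ends by promising P values too.
- **Multiplicity (2.13.2, last paragraph).** "In post hoc tests, we will employ the Bonferroni correction method". No divisor is given. The same sentence mentions adjusting for several outcomes and time points.

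**The concern.** The endpoint and sample size sections point to two specific comparisons at one visit. The testing sentence starts instead from an overall interaction over all visits and all groups, and treats the comparisons of interest as post hoc. Three things follow.

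1. The overall interaction is not a test of the week-5 endpoint. It responds equally to differences that appear only at week 10.
2. It can be non-significant when a week-5 contrast against waitlist is clearly significant.
3. Two adjacent sentences each lead to a week-5 P value, one conditional and Bonferroni-corrected, the other neither. If the interaction gave P = 0.08 and a week-5 contrast P = 0.01, the text would support either a negative or a positive claim on the primary endpoint.

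What is at stake is a decision rule that is not unique, plus some avoidable loss of power.

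**Working it through.** **Inputs.** Difference 2, SD 2.49, two-sided alpha 0.05, power 80%, 25 per group (2.13.1); 3 groups and visits at baseline, week 5 and week 10 (2.13.2).

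**Assumptions not in the article.** 2.49 is the SD of the change (the article does not label it); equal within-person correlation across visits; both active arms have the same effect; no missing data; no covariates.

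**1. The article's own figure.** n = 2(1.960 + 0.842)² × 2.49² / 2² = 24.3, so 25 per group. Normal-approximation power at 25: 2 / (2.49 × √(2/25)) = 2.84; 2.84 − 1.96 = 0.88, giving 81%. The stated 25 is reproduced, as one unadjusted pairwise comparison with no first stage.

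**2. Degrees of freedom.** Interaction: (3 − 1)(3 − 1) = 4. Error: 2 × (75 − 3) = 144.

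**3. Power of the interaction test.** The within-person residual variance is 2.49²/2 = 3.10. The noncentrality is λ = 25 × (sum of squared interaction effects) / 3.10.

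| True effect, week 5 / week 10 | Sum of squares | λ | P(interaction significant) |
|---|---|---|---|
| 2 / 2 | 16/9 | 14.3 | 86.3% |
| 2 / 1 | 4/3 | 10.8 | 73.5% |
| 2 / 0 | 16/9 | 14.3 | 86.3% |
| 0 / 2 | 16/9 | 14.3 | 86.3% |

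The last row shows that the test does not isolate week 5: it is significant just as often when nothing happens at week 5.

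**4. Cost of the condition alone.** Simulated power for one active arm versus waitlist at week 5, changing only whether a significant interaction is required first (60,000 trials per scenario):

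| Alpha for the contrast | Week-10 effect | No condition | With condition | Loss (points) |
|---|---|---|---|---|
| 0.05 | 2 | 80.5% | 75.6% | 5.0 |
| 0.05 | 1 | 80.6% | 68.3% | 12.3 |
| 0.025 | 2 | 71.7% | 69.0% | 2.7 |
| 0.025 | 1 | 71.8% | 64.4% | 7.5 |
| 0.05/3 | 2 | 66.2% | 64.5% | 1.6 |
| 0.05/3 | 1 | 66.2% | 61.2% | 5.0 |
| 0.05/6 | 2 | 56.7% | 56.1% | 0.5 |
| 0.05/6 | 1 | 56.7% | 54.8% | 1.9 |

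Losses are computed before rounding. With the effect gone by week 10, they match the fully maintained case.

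**5. How often the routes disagree at the same alpha.** At 0.025, at least one arm-versus-waitlist contrast is significant while the interaction is not in about 5% of trials (effect maintained) and 13% (half left). At 0.05 the figures are about 8% and 18%.

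**6. Sensitivity.**
- If 2.49 is the SD of the score and the within-person correlation is 0.7 (an assumption), the residual variance is 2.49² × 0.3 = 1.86. The interaction is then significant in 98% (effect maintained) or 93% (half left) of trials, and the loss at 0.05/3 is 0.3 to 1.8 points.
- With 30 per arm (no dropout) and SD of change 2.49, the interaction is significant in 92.5% and 82.2% of trials. The loss at 0.025 is 80.4 − 78.8 = 1.6 and 79.9 − 74.1 = 5.8 points.

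**The case against.** An overall test followed by adjusted pairwise tests is a common, conservative sequence for three arms, and the article condenses a fuller plan that may name the primary contrast. Three stronger criticisms are tempting, and none is supported.

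- **That a non-significant interaction leaves no permitted test of the primary endpoint.** The sentence after the conditional one promises week-5 differences with intervals and P values and attaches no condition. The text is ambiguous; it does not bar the comparison.
- **That an interaction driven by week 10 produces false week-5 findings.** It does not. Each contrast must still pass its own test. With an effect at week 10 only, the simulated week-5 error per contrast stays at or below its nominal level (2.5% at alpha 0.025).
- **That the condition explains the whole drop from 80% to about 61% to 65%.** Most of that drop is multiplicity adjustment. Going from 0.05 to 0.05/3 with no condition already takes power from about 80.5% to 66.2%; the condition adds 1.6 to 5.0 points. The divisor of 3 is itself an assumption, and the stricter the correction, the less the condition matters.

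What remains is that the article states a rule, and the next sentence states another. This is more than detail left to an analysis plan, because the two can give opposite answers on the primary endpoint.

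**Conclusion.** The point holds as a mismatch and an ambiguity, with a modest power cost; it is not a threat to validity. The first-stage test in 2.13.2 matches neither the week-5 endpoint in 2.9.1 nor the pairwise contrasts sized in 2.13.1, and the article does not say whether the conditional or the unconditional route decides. Since Bonferroni alone controls the error of the contrasts, the condition protects nothing that the correction does not already protect.

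The power cost rests on 25 per arm, SD of change 2.49 and equal 2-point effects at week 5. The low end of each range quoted in the summary applies if the effect persists to week 10, the high end if half is left. The cost shrinks with more patients, a larger Bonferroni divisor, or 2.49 read as the SD of the score with high within-person correlation. The change is worth making because it is nearly free and settles the decision rule.

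**What to change.** In 2.13.2, replace the conditional sentence with a statement that the primary analysis tests the week-5 contrasts of EA versus waitlist and EAWN versus waitlist directly from the mixed model, with a named multiplicity adjustment over these two and no requirement of a significant interaction. Report the overall interaction as supportive, and week 10 and EA versus EAWN as secondary. State that the week-5 differences, intervals and P values already promised are those of this primary analysis.

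The cost is one or two sentences, to be settled before the data are analysed, with no extra patients or measurements. The change does not restore the stated 80%: at 25 per arm, two contrasts each tested at 0.025 have about 72% power. That shortfall comes from the unadjusted alpha in 2.13.1 and is a separate point.

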**Discussion::**

Acupuncture and moxibustion could be potentially effective treatment alternatives for tinnitus. The study results will provide evidence to determine the efficacy and safety of electroacupuncture with or without warm needling for tinnitus.

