Acupuncture, one of the treatment modalities in traditional Chinese medicine (TCM) for tinnitus,^[9]^ has been widely used and recommended for tinnitus relief in China for a long time.^[10]^ The use of acupuncture for tinnitus was initially discussed in the Huangdi Neijing. Acupuncture and moxibustion can help relieve tinnitus by regulating the flow of blood and *qi*.^[10]^ Previous systematic reviews have shown promising results for manual acupuncture, electroacupuncture, or warm needling in reducing the loudness and disability of tinnitus.^[11–13]^ A Bayesian analysis showed that there was a trend of greater effectiveness of warm needling in the treatment of neurological tinnitus,^[14]^ but with limitations in study methodology and evidence.

To date, there is a lack of rigorous evidence for effective therapies to reduce or eliminate tinnitus. Further research on the therapeutic effects of acupuncture for tinnitus is warranted, and should be conducted according to higher methodological standards. Finally, given the importance of the health problem of tinnitus, a well-designed randomized controlled clinical trial is proposed.

Therefore, this study aims to explore and determine the efficacy and safety of electroacupuncture (EA) and electroacupuncture combined with warm needling (EAWN) for the treatment of subjective tinnitus among older adults in Hong Kong, and report the short-term follow-up results. We will compare the effects of the 2 acupuncture treatment groups and the control group in reducing the loudness of tinnitus and improving the impairment caused by tinnitus.

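### The only adverse event analysis stated for a declared safety aim is a significance test; a risk difference with a 95% confidence interval should be the main safety comparison

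*Protocol article*

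**What the plan says.** The Introduction sets the aim: "this study aims to explore and determine the efficacy and safety of electroacupuncture (EA) and electroacupuncture combined with warm needling (EAWN". The Discussion paragraph of the Abstract repeats it: "The study results will provide evidence to determine the efficacy and safety of electroacupuncture with or without warm needling for tinnitus".

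Section 2.13.2 (Statistical method and analysis) states one analysis for adverse events. It opens with "Comparisons between the EA and EAWN groups for the adverse event rate" and continues "for the adverse event rate among the 3 groups will be evaluated using the Pearson chi-squared test (or Fisher exact test". The threshold is common to all tests: "probability level of *P* < .05 with a 2-sided test throughout the analysis". The same section promises 95% confidence intervals as well as P values for the mean differences in the efficacy outcomes at weeks 5 and 10. It names no estimate or interval for adverse events.

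Section 2.13.1 sizes the trial on the loudness score only, for a "clinically significant difference of mean 2-point reduction and standard deviation of 2.49 in the NRS score of tinnitus loudness". Section 2.10 lists burns and blisters among the known events. It has each event recorded with timing, severity, management and causality. It gives no expected rates. Section 2.6.2 makes warm needling the only difference between the two active arms.

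**The concern.** A test of no difference answers the safety question only when it is significant. When it is not, the reader needs to know how large an excess the data still allow, and a P value does not show that. The EAWN versus EA contrast isolates the added risk of warm needling, for which burns and blisters are the obvious candidates. With 30 per arm, a sizeable excess of such events could easily give P >= .05. If only the test is reported, a wide range of possible harm could be passed over, and the safety half of the aim would be left with little usable evidence.

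**Working it through.** **Inputs from the protocol article.** Two-sided alpha 0.05 for every test (2.13.2). All randomized participants are analysed (2.13.2), so 30 per arm (2.13.1). Chi-squared or Fisher test, with no rule stated for choosing between them. Event rates are not given, so those below are assumptions shown as a range.

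**The plan's own figure.** Section 2.13.1: "Using a 2-sided test, an alpha value of 0.05, and a power of 80" percent, difference 2, SD 2.49.
n per group = 2 × (1.960 + 0.842)² × 2.49² / 2² = 2 × 7.85 × 6.20 / 4 = 24.3, rounded up to 25. Then 25 × 1.20 = 30. Both figures reproduce. Neither involves adverse events.

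**Significance boundary when EA has no events.** For k/30 against 0/30 the two-sided Fisher P is 2 × C(30,k) / C(60,k):
- k = 3: 2 × 4060 / 34220 = 0.237
- k = 5: 0.052
- k = 6: 0.024

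Fisher therefore needs at least 6 of 30. The uncorrected Pearson statistic is k² × 60 / [k × (60 − k)]:
- k = 3: 540 / 171 = 3.16, below the critical value 3.84
- k = 4: 960 / 224 = 4.29, P = 0.038

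Pearson therefore needs at least 4 of 30.

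**Power at 30 per arm.** With no events under EA, power is P(X ≥ 6) for Fisher or P(X ≥ 4) for Pearson, where X is binomial (30, EAWN rate). For non-zero EA rates, the probabilities of all pairs of counts with P < .05 are summed.

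| EA rate (assumed) | EAWN rate (assumed) | Fisher | Pearson |
|---|---|---|---|
| 0% | 10% | 7% | 35% |
| 0% | 15% | 29% | 68% |
| 0% | 20% | 57% | 88% |
| 5% | 15% | 9% | 26% |
| 5% | 20% | 24% | 45% |
| 10% | 20% | 10% | 19% |
| 10% | 30% | 37% | 50% |
| 20% | 40% | 30% | 39% |

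The lowest EAWN rate detected with 80% power (Fisher / Pearson) is 26% / 18% if EA is 0%, 36% / 31% if EA is 5%, and 44% / 41% if EA is 10%.

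**What an interval would show.** Take 3/30 in EAWN and 0/30 in EA. The Wilson 95% limits are 0.035 to 0.256 for 3/30 and 0 to 0.114 for 0/30. The Newcombe limits for the difference of 0.10 are:
- lower: 0.10 − √[(0.10 − 0.035)² + 0.114²] = −0.03
- upper: 0.10 + √[(0.256 − 0.10)² + 0²] = 0.26

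Neither test is significant, yet the data allow an excess of up to 26 percentage points. With 5/30 against 1/30, Fisher P = 0.19 and the difference is 13 points (−3 to +30). With 0/30 in one arm, the exact two-sided 95% upper limit is 1 − 0.025^(1/30) = 11.6%.

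**The case against.** The strongest reply has four parts.

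1. This is a journal article. Adverse event tables and their intervals are commonly left to the full protocol or analysis plan, so their absence here does not show that none are planned. This stands: the article cannot be faulted for an omission. The point concerns what it does state, namely a method and a threshold for a declared aim, in a section that promises intervals for efficacy.

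2. A reader might infer that any P >= .05 will be declared the trial's safety result. The documents do not support that. Section 2.13.2 says only when a result counts as significant, and no section treats non-significance as equal safety. Section 2.10 plans detailed recording of every event, so other safety evidence will exist.

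3. A reader might also infer that the test misses most relevant harms. That needs event rates and a threshold of relevance, and the protocol gives neither. It also depends on an unstated choice of test. With Pearson throughout, 0% versus 20% is detected 88% of the time, and even with Fisher more often than not (57%). At 0% versus 20% the expected count is about 3 events per arm, so the usual small-count convention would select Fisher, but the protocol does not say so. Low power for harms is also normal in a trial sized for efficacy and is not an error.

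4. Adding an interval supplies no margin, so there is still no decision rule. That is true. The purpose is to show what the data can and cannot exclude. A margin would need a clinical judgement for which the documents give no basis.

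**Conclusion.** The point holds as a cheap improvement to the stated method, not as a false statement in the protocol. For a declared safety aim, the article fixes a test without an estimate, at a sample size chosen for another outcome. A non-significant result would then carry little information about the added risk of warm needling. Under the assumed rates, power stays below 50% with either test for 0% versus 10%, 5% versus 20% and 10% versus 20%. Larger contrasts from a zero EA rate fare better, and the result there depends on the test chosen. The illustrative intervals do not depend on assumed rates or on the choice of test; they follow from 30 per arm and the example counts. The efficacy analyses are unaffected.

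**What to change.** In section 2.13.2, replace the adverse event sentence with text such as:

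> For each arm, the number and proportion of participants with at least one adverse event will be reported, overall and for burns or blisters, with exact (Clopper-Pearson) 95% confidence intervals. The main safety comparison will be the EAWN minus EA risk difference with a Newcombe 95% confidence interval. The chi-squared or Fisher P value will be descriptive. P >= .05 will not be taken as evidence of equal safety.

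Naming the contrast would also remove a separate ambiguity: the present sentence refers both to the two active arms and to all three groups.

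The cost is a few lines of text and one extra table column, with no extra participants, visits or data. The downside is a more modest safety claim, because the intervals will be wide.

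### Bonferroni for the post hoc group contrasts is valid, but Holm's step-down method keeps the same 5% bound and would show both acupuncture arms effective more often, at the cost of one phrase

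*Protocol article*

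**What the plan says.** Section 2.13.2 fits a linear mixed model to the three groups over baseline, week 5 and week 10. A significant time-by-group interaction leads to pairwise follow-up: significant results "will be subject to post hoc tests to determine which group scores differently". For that step the method is named: "In post hoc tests, we will employ the Bonferroni correction method". The same sentence extends the adjustment of the significance level across outcomes and time points. No step-down procedure is mentioned, and the number of comparisons covered by the correction is not given. The aim of finding which of three groups differ points to all three pairwise contrasts.

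Section 2.13.1 gives the scenario the trial is built on. It takes a "clinically significant difference of mean 2-point reduction and standard deviation of 2.49 in the NRS score of tinnitus loudness" and assumes "similar differences in the NRS score of tinnitus loudness will be detected between the EA and waitlist control groups or the EAWN and waitlist control" arms. So both active arms are expected to beat waitlist by about the same amount, and EA and EAWN are expected to be about equal.

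**The concern.** Ordinary Bonferroni holds every contrast to alpha/m, even after another contrast in the family has been rejected. Holm tests the smallest P value at alpha/m, the next at alpha/(m−1), and so on. The bound on family-wise error is the same and no assumption is added.

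The difference matters most when several effects are real, which is what section 2.13.1 assumes. Once one arm has been shown better than waitlist, Bonferroni still holds the other arm to the strict level. With 25 evaluable per arm, an effective second arm could be reported as non-significant although a procedure with the same error bound would have declared it.

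**Working it through.** **Inputs (section 2.13.1).** Difference 2 points, SD 2.49, two-sided alpha 0.05, 80% power, 25 per group before attrition, 30 after. Equal effects in both arms give true differences of 2 (EA vs waitlist), 2 (EAWN vs waitlist) and 0 (EA vs EAWN). I take 2.49 as the SD of the analysed week-5 score and ignore any precision gained from covariates or the mixed model.

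**1. The plan's own figure.** n = 2 × (1.960 + 0.842)² × 2.49² / 2² = 2 × 7.849 × 6.200 / 4 = 24.3, so 25 per group. This reproduces. Power at 25: SE = 2.49 × √(2/25) = 0.704; 2/0.704 = 2.840; Φ(2.840 − 1.960) = 81.1%, for one contrast at unadjusted 0.05.

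**2. The thresholds, P values ordered from smallest.**
- Two contrasts: Bonferroni 0.025, 0.025; Holm 0.025, 0.05.
- Three contrasts: Bonferroni 0.0167 each; Holm 0.0167, 0.025, 0.05; Shaffer 0.0167, 0.05, 0.05. Shaffer's version works because, with three means, once one pairwise null is false at most one of the other two can be true.

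**3. Power at week 5.** Simulation, 1,000,000 trials per case: 25 per arm, shared waitlist arm, pooled variance, 3 × 25 − 3 = 72 df.

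| Family | Procedure | Both arms beat waitlist | Each arm vs waitlist | At least one arm |
|---|---|---|---|---|
| Two vs waitlist | Bonferroni | 57.0% | 70.8% | 84.7% |
| Two vs waitlist | Holm | 67.7% | 76.2% | 84.7% |
| Three pairwise | Bonferroni | 50.1% | 65.2% | 80.2% |
| Three pairwise | Holm | 56.8% | 68.5% | 80.2% |
| Three pairwise | Shaffer | 66.0% | 73.1% | 80.2% |

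Gains for both arms: 67.7 − 57.0 = 10.7; 56.8 − 50.1 = 6.7; 66.0 − 50.1 = 15.9 points. Gains per contrast: 76.2 − 70.8 = 5.4; 68.5 − 65.2 = 3.3; 73.1 − 65.2 = 7.9 points. The last column does not move because the smallest P value faces the same threshold under every procedure.

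**4. Sensitivity.**
- 24 per arm (30 × 0.8): 54.5% to 65.4% (two contrasts, Holm); 47.6% to 54.3% (three, Holm) or 63.5% (three, Shaffer).
- 30 per arm: 68.2% to 77.6%; 61.8% to 68.2% or 76.3%.
- Requiring a significant overall F-test first, as a stand-in for the interaction test, leaves the Bonferroni and Holm figures essentially unchanged.
- If one family also spans week 10 (four or six contrasts), Holm's gain for both arms at week 5 runs from about 3 to 15 points. This assumes a week-10 effect of 0 to 2 points and a within-person correlation of 0.5 to 0.7, neither of which the protocol gives.

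**5. Error control.** With no true differences, family-wise error is 4.4% (three contrasts) and 4.6% (two) for both Bonferroni and Holm. Under the plan's scenario the only true null is EA versus EAWN. In the family of three it is falsely rejected in 1.7% of trials with Bonferroni, 3.3% with Holm and 4.9% with Shaffer. With very large true effects (5 points), Holm and Shaffer reach 5.0% and Bonferroni 1.6 to 1.7%. All stay within the bound.

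**The case against.** The strongest reply is that nothing here is wrong. Bonferroni is valid, prespecified and simple. It also gives matching simultaneous confidence intervals directly, which step-down tests do not, and section 2.13.2 promises 95% intervals without saying whether they are adjusted. That stands: this is a matter of efficiency, and wanting matching intervals would be a fair reason to keep Bonferroni.

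Four stronger readings are tempting, and the document does not support them.
- A reader might take 11 points as the loss. That needs a family of exactly two contrasts, which the protocol does not define. The three-group wording gives about 7 points with Holm.
- A reader might treat showing both arms effective as the trial's power target. Section 2.13.1 sizes each active arm against waitlist and sets no joint target. Per contrast the gain is 3 to 8 points.
- A reader might infer that Bonferroni buys no extra protection against false positives. The bound is the same, but the realised error is lower, as the EA-versus-EAWN rates show.
- A reader might apply Shaffer's thresholds throughout. They are valid only within the three contrasts of one outcome at one time point, while section 2.13.2 also adjusts across outcomes and time points. Run at full 0.05 separately at weeks 5 and 10, the family error with no true differences would be about 8.4% if the time points were independent; correlation would lower it.

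**Conclusion.** The point holds as a cheap efficiency improvement, not as an error in the plan. On the plan's assumptions at week 5, with 25 evaluable per arm, Holm lifts the chance of showing both arms better than waitlist from 57% to 68% (two contrasts) or from 50% to 57% (three). Shaffer's version lifts it to 66% in the three-contrast family.

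These sizes rest on equal 2-point effects in both arms, on 2.49 being the SD of the analysed score, and on a family limited to week 5. That Holm rejects at least as much as Bonferroni within the same bound rests on none of these. Section 2.13.1 sizes the trial at unadjusted 0.05, which is a separate matter; this point stands whether or not it is addressed.

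**What to change.** In section 2.13.2, name the Holm step-down method instead of Bonferroni for the post hoc group contrasts, applied to whatever family the plan adjusts over. If the three pairwise contrasts of one outcome at one time point form a family of their own, Shaffer's version may be used inside it: smallest P value against one third of the alpha allotted to that family, then the other two against that full alpha (0.05/3, then 0.05, when the allotment is 0.05). It should not be carried across outcomes or time points.

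State also whether the reported 95% intervals are unadjusted, since they will not match the step-down decisions exactly.

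The cost is one phrase and one sentence, settled before results are seen. No patients or data are added, and the procedure can be worked by hand from unadjusted P values. What is given up is simple simultaneous intervals and some unused margin below the 5% bound.
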